## Data safety and monitoring board

## Data safety will comply with the National Statement on Ethical Conduct in Human Research. Only the responsible clinicians, delegated research assistants, and Chief Investigator listed on this application will handle data.

## For the purposes of this study, the eCentreClinic will not collect personal identifying information. This will be collected by the MHA and stored in a password protected file in a password protected network.

## Early termination

If a participant wishes to withdraw from the study once it has started, he or she can do so at any time without having to give a reason. This process will be supervised by the MHA Psychologist. Upon early withdrawal, all participants will be provided with encouragement to access additional services via their GP. Additionally, all participants will be given the opportunity to provide feedback about their current symptoms. If participants withdrawing from the Course do report a deterioration of their symptoms, they will be contacted by a Psychologist or Chief Investigator to discuss access to additional services. If participants do not choose to provide feedback about their symptoms, but the investigators have concerns about the participant's condition, we do have consent from all participants to contact their GP.

# Blinding and unblinding

Study is not blinded.

# STATISTICAL CONSIDERATIONS

## Sample Size Calculation

With respect to power, a sample of 15 consumers, with power at 80% and alpha of 0.05, will be sufficient to detect a pre-post effect size difference of 0.7, which is the minimum difference expected based on previous studies at the eCentreClinic. However, to control for attrition, 20 participants will be recruited.

## Analysis Plan

Analyses will be conducted using intention-to-treat and completer models.

# Storage and archiving of study documents

Throughout the study, research investigators at the eCentreclinic will have access to non-identified data, while the MHA Psychologist will be able to identify participants. During the data analysis phase, non-identifiable data (i.e. coded data) will be used. At study completion, non-identifiable data will be written to a password protected database. To maintain participant privacy the eCentreClinic operates using a Secure Socket Layer to provide secure encryption of the eCentreClinic data. Additionally the database is firewall protected. Staff associated with the project are aware of, and will adhere to, the National Statement on Ethical Conduct in Human Research [8].

For the purposes of this study, the eCentreClinic will not collect personal identifying information. This will be collected by the MHA and stored in a password protected file in a password protected network.

# APPENDICES

11.1 Questionnaires

Questionnaires to be included in the project are:

- PHQ-9: Patient Health Questionnaire – Nine item, (Kroenke, Spitzer, & Williams, 2001)
- GAD-7: Generalized Anxiety Disorder-7 Item Scale (Spitzer, Kroenke, Williams, & Löwe, 2006)
- Things You Do Questionnaire (developed by the researchers)
- Recruitment Process and Interview Protocol

[figure not shown]
**Patient Health Questionnaire-9 Item (PHQ-9)**

[figure not shown]
**Generalized Anxiety Disorder-7 Item Scale (GAD-7)**

[figure not shown]

| Things You Do Questionnaire | | |
| --- | --- | --- |
| IN THE PAST WEEK, how many times have you: | | |
| **Response Options**  0 = Never  1 = Once  2 = Twice  3 = Three times  4 = Four or more times | | |
| 1 | Attended a social activity (e.g., meeting a friend)? | 0 1 2 3 4 |
| 2 | Praised yourself when you did something well? | 0 1 2 3 4 |
| 3 | Ate 2 healthy meals in a day? | 0 1 2 3 4 |
| 4 | Did something you enjoy (e.g. a hobby or recreational activity)? | 0 1 2 3 4 |
| 5 | Had something to look forward to each day? | 0 1 2 3 4 |
| 6 | Reminded yourself that you can only do your best? | 0 1 2 3 4 |
| 7 | Did something that you initially wanted to avoid? | 0 1 2 3 4 |
| 8 | Had at least 30 minutes of exercise? | 0 1 2 3 4 |
| 9 | Talked your problems through with a friend or family member? | 0 1 2 3 4 |
| 10 | Talked yourself out of negative thinking? | 0 1 2 3 4 |
| 11 | Had a good night’s sleep? | 0 1 2 3 4 |
| 12 | Did something to help you to relax (e.g., practiced breathing exercises, read a book, surfed the web, etc.)? | 0 1 2 3 4 |
|  |  |  |
|  |  |  |
|  |  |  |
|  |  |  |
|  |  |  |

## Recruitment Process and Telephone Interview

**Summary of Process**

1. Ethics has been approved
2. Awaiting confirmation of [name]'s registration as Psychologist
3. [name] to register trial on ANZCTR
4. Once registration confirmed, MHA to: Email potential applicants with Information and Consent Form. Specify timeframe for response before closing of applications.
5. MHA to contact consenting applicants to conduct telephone interview (below).
6. Aim of telephone call:
   1. Check inclusion criteria: Resident of Australia, 18-64 years of age,
   - Not currently participating in CBT for target symptoms,
   - A score above 4 on the GAD-7 (indicating at least mild anxiety),
   - Provides informed consent,
   - Access to a reliable internet connection
   1. Check exclusion criteria:
   - Severe depression (i.e. score > 22 on PHQ-9)
   - Suicidal intention or plan,
   - Principal problem not anxiety,
   - Principal problem are symptoms of OCD,
   - Acute psychosis
   1. Conduct risk assessment and manage safety, as required
   2. Provide information about study
7. Refer Ineligible applicants to be referred to appropriate services, and send email confirming directions
8. Successful applicants to receive email confirming start date of course
9. Aim for 15-20 eligible participants
10. [name] to visit eCC Friday before course begins to create usernames
11. [name] and [name] to login on start date to test dummy accounts.
12. [name] then launches course (start emails sent to participants + Step by Step Guide)
13. [name] to attend supervision sessions (for this Course) at eCC at mutually convenient times (possibly Tue/Thur)
14. [name]/[name] to modify materials to co-brand with MHA: Require permission from MHA for name/signature to use on emails, and MHA logo.
15. [name] to send spreadsheet to [name]
16. [name] to keep spreadsheet at MHA, password protected.
17. Aim to start trial in July, with 2-month follow-up finished November, submit December 2012.

**MHA Open Trial Telephone Interview**

- Hello it’s XXXXX calling from **the MHA …**

1. I’m calling to complete your application for the MHA online anxiety course. To complete your application I need to ask you some questions about your anxiety and your mood. These will probably take 15 minutes to complete, do you have the time right now?
2. First, I want to thank you for applying to our MHA Wellbeing Course. I know it’s quite difficult for most people to apply / takes a lot of courage to apply.
3. I’ll be doing a lot of the talking for this call, but please stop me anytime to ask questions or clarify anything. Is that ok?
4. To start I need to ask you some preliminary questions to check that the course will be suitable for you.

| 1. | Part of the criteria for the course is that you have reliable access to the internet. Do you have reliable access? | Yes | No |
| --- | --- | --- | --- |
| 2. | The internet course is an education course. It is designed to teach people how to manage symptoms of worry, and stress, and panic and anxiety. Does this sound suitable to you? | Yes | No |
| 3. | The internet course is designed for people for whom anxiety is the main concern. Are symptoms of anxiety your primary concern? | Yes | No |
| 4. | The internet course is not designed for people who have symptoms of OCD. Are symptoms of OCD your primary concern? | Yes | No |
| 5. | The internet course is not designed for people with acute psychosis, who are hearing voices, seeing things that other people don't, or believe things that other people don't. Do you have those symptoms? | Yes | No |
| 6. | The Course will begin on XX and will take 8 weeks. Have you got anything planned (e.g. moving house, surgery, holiday) that will interfere with your participation in the Wellbeing Course for more than 2 weeks over that time? | Yes | No |

**IF NOT SUITABLE:**

**Reason:** Unfortunately, this Course will not be suitable for you. *Refer to other sources.* ***Encourage:*** *I really encourage you to go to your GP for a referral to a psychiatrist or clinical psychologist – Medicare does cover 12 sessions per year with these health professionals. OR, other.*

**IF SUITABLE:**

“Now I’m going to start by asking you some questions about mood” (Commence PHQ-9)

**Patient Health Questionnaire-9 Item (PHQ-9)**

[figure not shown]

**Exclusion: If Total score > 22, immediately and conduct safety assessment (next page) and exclude. Else, administer GAD-7**

**IF NOT SUITABLE:**

**Reason:** Unfortunately, your symptoms of low mood or depression are really high, and we don't think you will benefit as much from this course. Then administer Safety Assessment.

This Course will not be suitable for you. *Refer to other sources.* ***Encourage:*** *I really encourage you to go to your GP for a referral to a psychiatrist or clinical psychologist – Medicare does cover 12 sessions per year with these health professionals. OR, other.*

**Safety Assessment: Compulsory for All**

Note, complete relevant sections for all applicants

- If low or no risk (defined as 'yes' to 'a', below), please advise about the following (**and tick**): If mood deteriorates or feels at risk:
  - Contact us
  - Talk to friend
  - BUT if at risk of suicide: Contact emergency/support services if feel suicidal/feel self-harm (Life Line: [name]) or 000.
- If elevated risk (PHQ-9 >9, Qn 9 score >1), complete the following

**“We’ve noted that you had some symptoms of depression OR said that you’ve had thoughts that you would be better off dead.”**

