## Exclusion criteria

(1) Severe depression (i.e. score > 22 on PHQ-9), suicidal ideation or plan (based on interview),

(2) suicidal intention or plan,

(3) principal problem not anxiety,

(4) principal problem are symptoms of OCD,

(5) acute psychosis.

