## Study Procedure risks

It is expected that adults with symptoms of anxiety will experience clinically significant reductions in the severity of their symptoms. It is also hoped that the techniques taught in the Courses will be applied by participants after the trial is completed, resulting in long term improved management of symptoms. However, because anxiety often develops in teenage hood and early adulthood, it is likely that most of participants will have experienced distressing levels of emotions for several decades. The Course Course encourages them to learn and practice techniques for managing symptoms and, in the short term, this often leads to an increase in levels of symptoms.

Our priority is to support participants to stay safe. Steps for doing this include:

At Application:

Applicants with severe symptoms of depression or suicidal ideation or plan (total score of >23 on the PHQ-9, a reliable and valid measure of the symptoms of depression, and interview by a Psychologist), will not be eligible to participate, and will be provided with written contact details of how to access urgent support and will be strongly encouraged to do so. Applicants assessed as having a principal disorder not targeted by the Courses will not be eligible for this study, as they are unlikely to benefit from the Course. Instead, they will be encouraged to consider other treatment options including accessing their GP or local services, and informed about more appropriate iCBT Courses which may target their specific problem.

During the telephone interview, all applicants are screened for risk of suicide or self-harm. Those at risk will not be eligible to participate, as we believe they require more immediate and intense support than can be provided via the Internet. Instead, they will be assisted to access urgent support from specialist crisis management services and this support will be followed up with written information.

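### The telephone screening form contradicts itself: every applicant must be checked for suicidal intention or plan, but its score trigger, read literally, lets some be accepted without being asked

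*Protocol*

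**What the plan says.** Three places in the protocol set the rule.

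- Section 4.2, Exclusion criteria, lists "suicidal ideation or plan (based on interview") in item (1) and "suicidal intention or plan" in item (2). Item (2) carries no PHQ-9 threshold.
- Section 5.3, Study Procedure risks, states: "During the telephone interview, all applicants are screened for risk of suicide or self-harm".
- The process summary in the Appendices (step 6) names "Suicidal intention or plan" among the exclusion criteria that the call is meant to check.

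The form that carries out the rule is in the Appendices under the heading "Safety Assessment: Compulsory for All". A note beneath it tells the caller to "complete relevant sections for all applicants". Two branches follow. One begins "If low or no risk (defined as 'yes' to 'a', below") and consists of advice only. The other begins "If elevated risk (PHQ-9 >9, Qn 9 score >1), complete the following", followed by a lead-in statement and then questions (a) to (d). Question (c) asks about intention or plan and is marked as an exclusion criterion.

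**The concern.** The rule covers all applicants, but the form ties the question that implements it to a depression score. An applicant below the trigger could complete the interview and receive the acceptance email without anyone having asked about intention or plan.

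Such applicants belong to the target population. Section 4.1 requires a GAD-7 score above 4 and sets no minimum on the PHQ-9, so an anxious applicant with few depressive symptoms is eligible. What is at stake is participant safety and the uniform application of an exclusion criterion. Power, estimation and analysis are unaffected.

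**Working it through.** The plan gives no figure to reproduce. The check is to follow the script as a decision tree and compare it with the rule.

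**Step 1: the way into the Safety Assessment.** After the PHQ-9, the script excludes totals above 22 and sends everyone else to the GAD-7 without mentioning the Safety Assessment. Later, after the Safety Assessment, suitable applicants are again sent to the GAD-7. The second instruction, together with the compulsory heading, implies the order PHQ-9, Safety Assessment, GAD-7. The first is therefore an ordering slip. The remaining steps assume the intended order.

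**Step 2: the trigger.** It names two conditions separated by a comma: a PHQ-9 total above 9, and an item 9 score above 1. The comma can mean AND or OR. The lead-in that follows refers to depressive symptoms or to thoughts of being better off dead, and joins the two with a capitalised OR, which favours OR. The table takes totals of 22 or less and assumes that item 9 is scored 0 to 3, because the questionnaire is not shown.

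| PHQ-9 total | Item 9 | (a)–(d) opened if OR | (a)–(d) opened if AND |
| --- | --- | --- | --- |
| 9 or less | 0 or 1 | No | No |
| 9 or less | 2 or 3 | Yes | No |
| 10 to 22 | 0 or 1 | Yes | No |
| 10 to 22 | 2 or 3 | Yes | Yes |

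The first row misses the questions under either reading. Under OR, the better-supported reading, it is the only row that does. It includes an applicant who scores 1 on item 9, because 1 does not exceed 1.

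**Step 3: is intention or plan asked anywhere else?** The Risk Assessment sheet has a line for current plan or intent. Its three listed reasons for use correspond to answers to (b), (c) and (d), so on a literal reading it lies behind the same trigger. The preliminary questions at the start of the call cover internet access, suitability, anxiety as the main concern, OCD, psychosis and availability. None concerns self-harm.

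**Step 4: the last gate.** A GAD-7 score below 5 ends the interview. Otherwise the confirmation email is sent. An applicant with a PHQ-9 total of 9 or less, item 9 of 0 or 1 and a GAD-7 score of 5 or more can therefore be accepted without being asked (c).

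**Step 5: the form's own definitions.** Low or no risk is defined first by a yes to (a), and again below the table by a yes to (a) alone. The second definition presupposes that (b), (c) and (d) were asked. An applicant below the trigger has answered none of these, so the form cannot classify that person by its own terms. Elevated risk also has two meanings: a PHQ-9 score in the trigger, and a yes to (c) or (d), with exclusion, below the table.

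**The case against.** The strongest reply is that the form intends everyone to be asked. The heading says so, and both low-risk definitions depend on answers to the questions. The trigger might govern only the lead-in, which suits only applicants with symptoms. As a reading of intent this stands, and it is why the point is a contradiction in the form. It does not settle what the caller should do: the note limits completion to relevant sections, and the only stated test of relevance placed before the questions is the score.

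A second reply is that screening is stepped. The PHQ-9 is given orally by a psychologist, so item 9 is part of the interview, and the process summary asks for a risk assessment only where needed. Part of this stands: item 9 may satisfy the general statement in section 5.3 that all are screened. But the lead-in paraphrases item 9 as thoughts of being better off dead, which is not intention or plan. The conditional wording in the process summary belongs to the separate risk-assessment line, not to the list of exclusion criteria to be checked.

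A third reply points to safeguards: a registered psychologist trained to manage risk, crisis advice to all applicants, PHQ-9 checks before each lesson, and contact on deterioration or lack of improvement. These reduce possible harm. The advice and monitoring do not apply the entry criterion.

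A reader might infer that all low PHQ-9 scorers escape the question, or that at-risk people would in fact be enrolled unasked. The documents support neither. Under OR, a low total with item 9 of 2 or 3 still reaches (c), and a psychologist may well ask everyone.

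**Conclusion.** The contradiction is real and should be corrected. The protocol requires a check for suicidal intention or plan in every applicant. The form, read literally, omits the only scripted screening question on it for those with a PHQ-9 total of 9 or less and item 9 of 0 or 1. This holds under either reading of the comma.

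The conclusion rests on taking the trigger to cover the whole block of questions, which is the literal sense of the instruction but probably not what the authors intended. The share of applicants affected cannot be derived, because the protocol gives no distribution of PHQ-9 scores among callers. Counting possible score combinations would not supply it. The conflicting time windows in question (d) are a separate matter and add nothing to this point.

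**What to change.** - State on the form that (c) is asked of every applicant, whatever the PHQ-9 score.
- Change the routing after the PHQ-9 to: *Else, complete the Safety Assessment, then the GAD-7.* This matches the compulsory heading and the later instruction.
- If a score trigger is kept for the other questions, write OR in place of the comma. Do not label it elevated risk, since the form also uses that term for a yes to (c) or (d).

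The cost is a few words on the form and a little more time in a call that is already planned. A few more applicants may be excluded. Question (c) asks about self-harm, which is broader than the suicidal intention or plan named in section 4.2, but section 5.3 also makes those at risk of suicide or self-harm ineligible. Any extra exclusions would therefore be of people whom one of those two sections already rules out.

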**“A lot of people have difficulty with depression. Some of these people have thoughts of harming themselves”**

| a | In the past 12 months have you had any thoughts that life is not worth living? | No | Yes |
| --- | --- | --- | --- |
| b | In the past 12 months have you had thoughts of harming yourself? | No | Yes |
| c | Do you have any intention or plan of harming yourself? (exclusion criteria) | No | Yes |
| d | In the past 5 years have you ever made any suicide attempts or harmed yourself in anyway? (active suicidal intention (6 months + risk assessment) and recent (12month self harm) = exclusion criteria) | No | Yes |
| If YES to question (c) or (d), exclude, but conduct risk assessment, develop management plan, and document actions and then follow-up with applicant. If NO, continue interview | | | |

- If low or no risk (defined as Yes only to (a)): discuss steps to take if mood deteriorates, as above
- If elevated risk (defined as 'yes' to Qns (c) or (d)), applicant is to be excluded, but conduct risk assessment, develop management plan, and document actions and then follow-up with applicant. If NO, continue interview

**“I’m quite worried about you, it sounds like you are feeling really down. I'd like to ask you more questions**

| **RISK ASSESSMENT** | | | | | | | | |
| --- | --- | --- | --- | --- | --- | --- | --- | --- |
| **Applicant/Participant Name:** | | | | **Date/Time:** | | | | |
| **eCentreClinic Team Member:** | | | | **DOB**: | | **Sex** | |  |
| **Guidelines**   1. **Conduct abbreviated risk assessment** 2. **Develop safety plan in consultation with applicant (document):** 3. **If possible, consult with VirtualClinic clinicians (document)** 4. **Refer to appropriate services: GP, Emergency, Hospital, Lifeline (document)** 5. **Negotiate follow-up with applicant (document)** 6. **Discuss with**  **Principal Investigator (document)** | | | | | | | | |
| **REASON FOR RISK ASSESSMENT (Tick):**  **[ ] Thoughts of harming self in last 12 months**  **[ ] Intention to commit suicide or self-harm?**  **[ ] Stated has made previous attempts at suicide or self harm** | | | | | | | | |
| **SUICIDE** | | | | | | | | |
| **Background factors** | *Y=Yes, N=No, UK=Unknown* | | **Current factors** | | *Y=Yes, N=No, UK=Unknown* | | | |
| Previous suicide attempts | | [ ] Y [ ] N [ ] UK | Recent significant life events | | | | [ ] Y [ ] N [ ] UK | |
| History of other self harm | | [ ] Y [ ] N [ ] UK | Hopelessness/despair | | | | [ ] Y [ ] N [ ] UK | |
| Family history of suicide | | [ ] Y [ ] N [ ] UK | Expressing high levels of distress | | | | [ ] Y [ ] N [ ] UK | |
| Separated/widowed/divorced | | [ ] Y [ ] N [ ] UK | Expressing suicidal ideas | | | | [ ] Y [ ] N [ ] UK | |
| Isolation/lack of role | | [ ] Y [ ] N [ ] UK | Self-harming behaviour | | | | [ ] Y [ ] N [ ] UK | |
| Other *(specify)* | | [ ] Y [ ] N [ ] UK | Current plan/intent | | | | [ ] Y [ ] N [ ] UK | |
|  | |  | Other *(specify)* | | | | [ ] Y [ ] N [ ] UK | |
| **Summary Notes and Safety Plan (by administering Clinician) (Risk, Protective, Previous attempts, Referred, Safety Plan, Information Provided, other)**  ......................................................................................................................................................................................  ......................................................................................................................................................................................  ......................................................................................................................................................................................  ......................................................................................................................................................................................  Name ………………………………. Signature ……………………………….. Date ……………..  Chief Investigator Review/Notes:  ......................................................................................................................................................................................  ......................................................................................................................................................................................  Name ………………………………. Signature ……………………………….. Date …………….. | | | | | | | | |

